## Abstract

**Introduction::**

The prevalence of lumbosacral radiculopathy is estimated to be approximately 3% to 5% in patient populations. Lumbosacral radiculopathy is largely caused by a complex interaction between biomechanical and biochemical factors. Nerve block therapy (NBT) mainly treats lumbosacral radiculopathy by improving the biochemical factors, whereas acupotomy mainly focuses on improving the biomechanical factors. Therefore, it is thought that synergistic effects may be obtained for the treatment of lumbosacral radiculopathy when both NBT and acupotomy are combined. However, no study in China and Korea, where acupotomy is majorly provided, has reported the effects of such a combination treatment. Therefore, this study aimed to evaluate the safety, effectiveness, and cost-effectiveness of the concurrent use of a deeply inserted acupotomy and NBT for the treatment of lumbosacral radiculopathy.

**Methods/design::**

This is an open-label, parallel, assessor-blinded, randomized controlled trial, which will include 50 patients with lumbosacral radiculopathy. After patients voluntarily agree to participate in the study, they will be screened, and will undergo necessary examinations and tests according to the protocol. Those who satisfy the selection criteria will be randomly assigned to either the NBT + acupotomy or NBT groups in a 1:1 ratio. Both groups will undergo 2 NBTs once every 2 weeks from 1 week after the screening test. The treatment group will receive additional acupotomy twice a week for 4 weeks. The primary endpoint is the Oswestry Disability Index, whereas the secondary endpoints are the Numeral Rating Scale, European Quality of Life 5-dimension, McGill pain Questionnaire, Roland-Morris Disability Questionnaire, safety assessment, and economic feasibility evaluation. The measurements will be made at 0, 2, 4, and 8 weeks.

**Ethics and dissemination::**

This trial has received complete ethical approval from the Ethics Committee of Catholic Kwandong University International St. Mary's Hospital (IS20OISE0085). We intend to submit the results of the trial to a peer-reviewed journal and/or conferences.

## Introduction

1

Although the literature lacks concise epidemiologic data, it is estimated by most reports that the prevalence of lumbosacral radiculopathy is approximately 3% to 5% in patient populations. Moreover, the condition constitutes a significant reason for patient referral to either neurologists, neurosurgeons, or orthopedic spine surgeons.^[1]^

Lumbosacral radiculopathy is the clinical term used to describe a predictable constellation of symptoms occurring secondary to mechanical and/or inflammatory cycles compromising at least one of the lumbosacral nerve roots.^[2]^ Patients can present with radiating pain, numbness/tingling, weakness, and gait abnormalities across a spectrum of severity. Depending on the nerve root(s) affected, patients can present with these symptoms in predictable patterns affecting the corresponding dermatome or myotome.

Lumbosacral radiculopathy is largely caused by complex interactions between biomechanical and biochemical factors.^[3]^ Biomechanical factors mainly cause continuous neuromuscular compression, which damages micro blood flow to the nerves and thereby activates C-fibers causing pain. Biochemical factors cause nerve damage by exposing phospholipase A2 to the surrounding nerves, leading to the production of various pathological substances that spread to the surrounding nerve roots, endings, and receptors to cause pain.

In nerve block therapy (NBT), a mixture of steroids and local anesthetics is administered to control pain through anti-inflammatory actions on inflammatory nerve roots and surrounding tissues.

Acupotomy is a special type of acupuncture that involves the addition of a scalpel function to the existing acupuncture needle. Since the tip of the acupotomy needle is a flat blade that can also function in synechotomy, the effects of both acupuncture and surgical treatment are expected from the procedure.^[4,5]^ Consequently, acupotomy treatment has been applied for various musculoskeletal diseases.^[6–11]^ Moreover, in China where acupotomy-related studies are actively being conducted, a total of 36 randomized controlled trials (RCTs) on lumbar disc herniation were published between 2006 and 2016,^[12]^ and 5 RCTs related to lumbar spinal stenosis were reported until 2017.^[13]^

However, in both China and Korea, there is no study on the effects of using both acupotomy and NBT as a combination treatment for lumbosacral radiculopathy.

Therefore, herein, we expect that the biochemical effects of NBT and the biomechanical effects of acupotomy will lead to a synergistic effect, and thereby propose to conduct a preliminary clinical study using the following protocol. The proposed study is expected to greatly contribute to the Korean and modern medicine combination treatment for lumbosacral radiculopathy and have important clinical implications.

### Objective

1.1

The study aims to verify the hypothesis that the concurrent use of a deeply inserted acupotomy needle and NBT is more effective, safe, and cost-effective for lumbosacral radiculopathy than NBT alone.

### Ethics and dissemination

1.2

This trial has received complete ethical approval from the Ethics Committee of Catholic Kwandong University International St. Mary's Hospital (IS20OISE0085). The findings in this study will be disseminated through peer-review journals and/or conference presentations.

## Materials and methods

2

### Trial registration

2.1

This study has been registered in the Clinical Research Information Service (CRIS, www.cris.nih.go.kr) (Trial registration number: KCT0006158; protocol version 1.3).

### Study design

2.2

This study is designed as a randomized controlled, 2-arm, parallel, and assessor-blinded study. The study will be conducted at the Catholic Kwandong University, International St. Mary's Hospital, Incheon, South Korea. The clinical trial and the items to be examined in this study are presented in Figure 1 and Table 1. The patients will receive a full explanation of the details of the trial from the investigators. Through this procedure, if they agree to participate in the trial, a signed consent form will be provided.

**Figure 1 F1:**
[figure not shown]
Study flow chart.

**Table 1 T1:** Clinical trial schedule and observation items.

Period		Screening^∗^ and Baseline	Treatment										Post Treatment	Early termination
Visit	Acupotomy + NBT group	Visit 1	Visit 2	Visit 3	Visit 4	Visit 5	Visit 6	Visit 7	Visit 8	Visit 9	Visit 10	Visit 11	Visit 12	Drop-out
	NBT group	Visit 1			Visit 2		Visit 3			Visit 4		Visit 5	Visit 6	
Day		0	1–3	4–6	7–8	9–11	12–14	15–17	18–20	21–22	23–25	26–28	56–58	
Written consent form		√												
Demographic survey		√												
Medical history, other medical history, and medication administration history		√												
Screening test^†^		√												
Selection/exclusion criteria		√												
Randomization (assignment of registration number)		√												
Physical examination and evaluation of vital signs		√	√	√	√	√	√	√	√	√	√	√	√	√
Medication administration history evaluation^‡^			√	√	√	√	√	√	√	√	√	√	√	√
Treatment	+ Acupotomy (combination treatment group)		√	√		√	√	√	√		√	√		
	NBT (all patients)				√					√				
Primary endpoint evaluation^§^		√					√					√	√	√
Secondary endpoint evaluation^||^		√					√					√	√	√
Exploratory efficacy evaluation^¶^													√	√^#^
Economic feasibility evaluation – cost evaluation^∗∗^		√					√					√	√	√
Adverse reaction monitoring			√	√	√	√	√	√	√	√	√	√	√	√
Economic feasibility evaluation – safety evaluation^††^			√	√	√	√	√	√	√	√	√	√	√	√

∗ One and 2 weeks are required from screening test to active treatment for combination treatment and NBT single treatment groups, respectively.

† Blood test [CBC 5 types, AST, ALT, ALP, albumin, BUN, protein, creatinine, total cholesterol, fasting glucose, RA, CRP, ASO, ESR, electrolyte 4 types (Na, K, Cl, T- CO_2_)]. It can replace test values performed within 8 weeks from screening.

‡ Concomitant medication history and adverse events monitoring are conducted at every visit for treatment and assessment.

§ ODI assessment.

|| Lower back and lower extremity pain (NRS) related to sacral neuropathy, quality of life (European Quality of Life 5 Dimension), Korean version of shortened MPQ, and Korean version of RMDQ.

¶ Additional NBT or surgical treatment within 4 weeks of the final procedure.

# Exploratory evaluation is not conduced for patients who have completed treatment early. For patients who dropped out of the study, exploratory evaluation is conducted after 4 weeks from dropping out (exploratory effectiveness evaluation for dropout participants can be conducted through telephone counseling instead of in-person visits).

∗∗ Evaluation of direct non-healthcare, direct non-healthcare, and lost productivity costs.

†† Those patients who reported adverse reactions will complete EQ-5D by recalling time of adverse events.

Patients who undergo 1 NBT and show continued symptoms (patient's subjective pain improvement is less than 50% after the procedure or the numeric rating scale (NRS) score being 5 or higher) will undergo screening at 1 week after the first procedure. For screening, demographic information, medical history, physical examination, vital signs, questionnaire survey, laboratory test, and selection/exclusion criteria will be evaluated. Randomization and group allocation will be performed at screening and baseline. Fifty patients will be enrolled and randomly divided into 2 groups. Patients who are judged suitable for the study after the screening test and voluntarily agree to participate will be randomly assigned to either the NBT single treatment group (usual care group) or NBT + deeply inserted acupotomy treatment group in a 1:1 ratio (Fig. 1). Thereafter, the randomly assigned patients will undergo primary and secondary outcome evaluations and economic evaluation.

The NBT + deeply inserted acupotomy group will receive 8 acupotomy treatments (at visits 2, 3, 5, 6, 7, 8, 10, and 11) for 4 weeks as well as additional 2 NBTs (at visits 4 and 9) for 4 weeks. Then, the group will be followed-up for 4 weeks after the intervention treatment. The standard care group will undergo two NBTs (at visits 2 and 4) for 4 weeks and will be followed-up for 4 weeks after the intervention treatment. Primary and secondary outcomes, economic evaluation, and assessment of drug administration history will be conducted at visits 1, 6, and 11, and at the end of follow-up. To evaluate safety, evaluation of adverse events, vital signs, and economic feasibility will be conducted at every visit from visit 2 to visit 12. Laboratory tests will be conducted only at screening.

Face-to-face evaluations will be conducted during the study period in parallel with the clinical trial. Then, face-to-face evaluations, distribution-type surveys, telephone surveys, or online meeting may be conducted after treatment period.

The coordinators of the trial will inform the patient of the next visit schedule for each visit and encourage participation. The clinical trial conductor will instruct the participant to ensure compliance with the treatment.

Only patients who have completed the informed consent form with full acceptance of the expected effects and predicted adverse reactions to the clinical trial interventions prior to commencement of the study may participate in the study. In the event of an accident or adverse event, appropriate measures will be taken according to the investigator's judgment and the participant will be compensated. Moreover, the study will be conducted ethically, in compliance with the principles of the Good Clinical Practice (GCP) guidelines and the revised version of the Declaration of Helsinki.

### Sample size calculation

2.3

This is a practical clinical study to assess the effects NBT and deeply inserted acupotomy combination treatment on lumbosacral radiculopathy.

In a previous pilot RCT that compared the therapeutic effects of deeply inserted acupotomy and general acupuncture in lumbar disc herniation patients,^[14]^ considering a 20% drop-out rate, a total of 50 patients (25 each in the acupuncture and deeply inserted acupotomy groups) were included.

In another RCT that compared the effects of deeply inserted acupotomy and general acupuncture in lumbar disc herniation patients,^[15]^ a total of 40 patients (20 each in the acupuncture and deeply inserted acupotomy groups) were included.

The phase 1 preliminary clinical study that will be conducted aims to estimate the mutual effects of NBT and deeply inserted acupotomy combination treatment and assess whether the combination treatment is effective and safe compared with conventional treatment. Thus, the study must be conducted with a minimum number of patients within the limit that satisfies the study purpose. Currently, there is no previous study that has provided the same intervention. Therefore, based on previous studies that provided similar treatment interventions and involved disease groups as in our study, 20 patients were included in each group. Considering a dropout rate of 20%, a total of 50 patients (25 patients in each group) was set as the target sample size.

### Intervention

2.4

#### NBT

2.4.1

1.Drugs used in NBT (5–10 ml mixture of the following drugs)Dexamethasone sodium phosphate 2.5 mg0.3% MepivacaineHyaluronidase 1500 IU2.Nerve block method3.As long as there is no problem with safety based on the actual nerve block treatment method, the treatment site, dose, and method can be freely selected based on the discretion of the practitioner.4.The type of NBT is the epidural block (epidural steroid injection) using the following approaches: interlaminar approach, transforaminal approach, caudal block, etc.5.Number of treatments6.Once every 2 weeks, a total of 2 times.

#### Acupotomy therapy

2.4.2

1.Treatment tools2.0.7∗50 mm or 0.70∗80 mm-sized needles (Hansung, Korea) will be used in this study.3.Number of treatments4.Twice a week for 4 weeks, a total of 8 times after visit 2.5.Treatment method(1)Application of an ice pack on low back skin for less than 20 minutes before the procedure to reduce pain.(2)Disinfection of the treatment area with alcohol, followed by povidone.(3)Performance of acupotomy on the disinfected treatment area. Consultation with experts to ensure safety during the procedure and conduction of ultrasound-guided acupotomy for standardized procedures. The detailed treatment areas and methods are shown in Supplementary Digital Content Appendix 1.(4)After the procedure, the treatment area is pressed for hemostasis using a sterile gauze for 3 minutes, and the area is covered with band-aids.(5)All patients must remain under observation for 15 minutes for any potential side effects and undergo education for prevention of infection in the treatment area and pain management before leaving.

### Inclusion and exclusion criteria

2.5

#### Inclusion criteria

2.5.1

The inclusion criteria are as follows:

1.adult men and women aged 18 to 85 years;2.patients diagnosed with spondylosis with lumbosacral disc disorder (injury), spinal stenosis, or lumbosacral radiculopathy through radiological examination (magnetic resonance imaging or computed tomography) within 6 months prior to participation in the clinical trial (in case of patients suspected of lumbosacral radiculopathy but with no imaging records at the time of screening test, magnetic resonance imaging or computed tomography scans will be performed to check whether they meet the diagnostic criteria);3.patients with symptoms related to lumbosacral radiculopathy, such as radiological pain, muscle weakness, and paresthesia of the lower extremities or those diagnosed with radiculopathy of the lumbosacral spine through a physical examination;4.patients who will undergo NBT within 2 weeks after the start of the clinical trial, and patients whose subjective pain improvement will be less than 50% after the procedure or the NRS score will be 5 or higher;5.patients who can read, understand, and answer the symptom questionnaire; and6.patients who volunteer to participate and give their written consent while agreeing to the clinical trial plan and follow-up.

#### Exclusion criteria

2.5.2

The following patients would be excluded from participating in the trial:

1.patients with a history of spinal surgeries, such as lumbar spine intrametallic fixation and spinal fusion, or those who have undergone past spinal surgery but continue to have related pain;2.patients with cauda equina syndrome or motor paralysis and neurological symptoms, which are expected to be difficult to treat with conservative therapy and require surgical treatment;3.patients taking drug treatments, such as strong opioid therapy, for pain control;4.Patients who received acupotomy treatment within 2 weeks before the start of the clinical study (inclusion will be permitted despite treatment at another institution within the relevant period for reasons different from the indications defined for this clinical trial at the discretion of the clinical trial practitioner);5.patients who have experienced side effects or hypersensitivity reactions after NBT in the past;6.patients with acupuncture hypersensitivity, metal allergy, severe atopy, keloid skin, and other skin sensitivities;7.patients with hemophilia;8.patients who are taking drugs that can cause hemostasis, such as anticoagulants, antiplatelet drugs, aspirin, etc., wherein it is not possible to stop the drug during the clinical trial period, according to the judgment of the clinical trial practitioner;9.patients who participated in other clinical studies within 30 days prior to the screening of the current clinical study and received investigational drugs, including placebos;10.patients with psychotic disorders, alcoholics, and drug addicts;11.pregnant women, lactating women, and women of childbearing potential who are not willing to use contraception during the clinical trial; and12.patients who are judged to be inappropriate for participation in clinical trials by the clinical trial practitioner.

### Recruitment, randomization, blinding, and nonblinding

2.6

Advertisements for patient recruitment will be posted on the Catholic Kwandong University, International St. Mary's Hospital's bulletin boards, along with posters, banner advertisements, and internet cafes. All advertisements will be run after institutional review board (IRB) approval.

Individuals who provide written consent to participate in the study will be assigned a screening number, according to the order of the outpatient visit at screening. Unblinded sub-investigators, who do not influence the research results and analysis, will refer to the randomization list that has been prepared by a commissioned professional statistician, and assign participation numbers. Participants will be allocated to the NBT group and the acupotomy + NBT group in a ratio of 1: 1. A block randomization table will be generated by an independent statistician and patients will be assigned to one of 2 groups according to the randomization table. Screening numbers, randomization numbers, and initials assigned to each participant will be used as subject identification codes to identify the participant until the end of the clinical trial.

The NBT used in this study is not a clinical investigational product and does not require allocation concealment, since it is administered to all groups. Moreover, it is impossible to blind the investigator and the participant in each group due to the nature of the study intervention, which is based on the contact between the patient and the medical staff. Instead, the investigator maintains blinding to prevent bias in evaluating the participant. After the clinical trial is completed, all clinical report forms (CRFs) will be collected, the database process terminated, and unblinding performed, if required for statistical analysis. Moreover, if it is deemed necessary to confirm the subject group due to an emergency situation during the clinical trial, the randomization code will be disclosed only to the participant, according to the principal investigator's discretion. If it is not possible to consult with the principal investigator and the situation is urgent, the randomization code of the subject will be disclosed after consultation with the randomization code officer. If unblinding is performed, the documentation of the reason for the unblinding will be retained, and the participant with the disclosed randomization code will not be able to continue the trial.

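### Section 2.6 confuses allocation concealment with masking of a shared treatment, and states no barrier between the block randomization list and the staff who enrol patients

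*Protocol article*

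**What the plan says.** The article's only statement on concealment is in section 2.6: the NBT "is not a clinical investigational product and does not require allocation concealment, since it is administered to all groups". The sentence after it turns to masking and says that "it is impossible to blind the investigator and the participant in each group due to the nature of the study intervention".

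The same section describes assignment:

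- The sequence: "A block randomization table will be generated by an independent statistician and patients will be assigned to one of 2 groups according to the randomization" (that is, the block list). The ratio is 1:1 and no block size is given.
- The people: "Unblinded sub-investigators, who do not influence the research results and analysis". These sub-investigators "will refer to the randomization list that has been prepared by a commissioned professional statistician, and assign participation numbers".

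The abstract describes the design: "This is an open-label, parallel, assessor-blinded, randomized controlled trial, which will include 50 patients with lumbosacral radiculopathy". Section 2.2 names one hospital and places randomization at the screening and baseline visit; Table 1 also shows the eligibility check at that visit. Section 2.5.2 leaves some exclusions to the practitioner's judgment (items 4, 8 and 12).

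On the order of events within visit 1, section 2.2 describes random assignment and continues: "Thereafter, the randomly assigned patients will undergo primary and secondary outcome evaluations and economic evaluation". Sections 2.8.1 and 2.8.2 attach the week-0 ODI, NRS, EQ-5D, MPQ and RMDQ to the screening test.

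**The concern.** Masking and concealment are different protections. Masking hides which treatment a patient is receiving. Concealment hides which treatment the next patient will receive until that patient is irrevocably in the trial. Masking is infeasible here for patients and treating staff; concealment is feasible in almost any trial, including an open-label one. That both arms receive NBT has no bearing on it, because the arms differ by acupotomy.

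If someone who knows the next allocation can also influence whether a patient enters, or when, the arms can come to differ in prognosis. Adjustment for baseline ODI in the primary analysis would remove only the part of that difference that baseline ODI captures. The trial is open-label with a self-reported primary endpoint, so concealed randomization is one of the few protections against bias that remain available.

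A lesser issue is the order of events at visit 1. Baseline ODI enters the primary analysis twice, in the change score and as the covariate. If patients reported it after learning their arm, the report could be affected by that knowledge.

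**Working it through.** **The plan's own figure.** Section 2.3 takes 20 per group and 20% dropout: 20 / (1 − 0.20) = 25 per group, 50 in total. This reproduces, and nothing below changes it.

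**Does any stated safeguard protect enrolment?**

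- The independent statistician protects generation of the sequence, not its concealment afterwards.
- The sub-investigators are said not to influence results and analysis. Screening, consent and eligibility are not mentioned.
- Blinded assessment acts after allocation.
- The randomization code officer in section 2.6 appears only in connection with emergency disclosure of a code already assigned.

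None of these separates the list from the decision to enrol.

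**How predictable is the next assignment?**

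1. With access to the list, the next allocation is known, whatever the block size.
2. Without it, take an open-label site where staff see past assignments. The block size is not in the document, so fixed sizes of 2, 4 and 6 are assumed. For a 1:1 permuted block of size 2h:
   - share of assignments certain from earlier ones = 1/(h + 1);
   - share guessed correctly by always naming the under-represented arm = [h + (4^h / C(2h, h) − 1)/2] / (2h).

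| Assumed block size | Certain | Guessed correctly | Of 50: certain | Of 50: correct |
|---|---|---|---|---|
| 2 (h = 1) | 1/2 = 50% | [1 + (4/2 − 1)/2] / 2 = 75.0% | 25.0 | 37.5 |
| 4 (h = 2) | 1/3 = 33.3% | [2 + (16/6 − 1)/2] / 4 = 70.8% | 16.7 | 35.4 |
| 6 (h = 3) | 1/4 = 25% | [3 + (64/20 − 1)/2] / 6 = 68.3% | 12.5 | 34.2 |

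Enumeration of all permuted blocks gives the same values. Chance alone gives 25 correct of 50. The last two columns apply the per-block share to 50 patients and ignore a final incomplete block. With larger fixed blocks the figures fall slowly: at size 10, 16.7% are certain and 65.3% are guessed correctly.

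**Order of baseline and allocation.** Two readings are open:

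- Allocation first: in section 2.2, the sentence that follows random assignment sends the assigned patients on to outcome evaluations, and Table 1 shows randomization and the first ODI at the same visit.
- Baseline first: sections 2.8.1 and 2.8.2 tie the week-0 measures to the screening test, section 2.2 lists a questionnaire survey among the screening items, and the abstract puts screening and tests before assignment.

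The text does not settle which is meant.

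**The case against.** The strongest reply is that the sentence is about NBT, not about the sequence. The article never says that the sequence need not be concealed, and the surrounding paragraph is about masking. The list comes from an independent statistician and is consulted by a designated unblinded role. Envelopes, web release and block sizes are details that an article normally leaves to the full protocol. The study is described as preliminary.

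Much of this is fair. The literal subject is NBT, and missing detail on block size or release mechanism is no fault in itself. The under-50% improvement criterion and the NRS threshold are patient-reported, so they give staff less leverage than the practitioner-judgment items do. What remains is that the only sentence on concealment gives a reason that is wrong for this trial, and the procedure described next sends trial sub-investigators to the list with a safeguard that does not cover enrolment. That is stated text, not omission. Being preliminary does not remove the need: section 2.3 still aims to assess effectiveness against conventional treatment.

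Three stronger readings are tempting and not supported:

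- A reader might infer that the list is open to all staff. The text shows only that the unblinded sub-investigators consult it.
- A reader might infer that those sub-investigators also screen or enrol, so that enrolment will be selective. The text does not say who enrols.
- A reader might infer that baseline ODI is collected after patients know their arm. The screening-test wording in sections 2.8.1 and 2.8.2 points the other way; only the order within the visit is unclear.

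**Conclusion.** The point holds in limited form. Section 2.6 confuses masking of a common treatment with concealment of the next acupotomy assignment, and the procedure it describes does not protect enrolment. Foreknowledge and selection bias are possible; the document does not show that they will occur, and no effect on ODI can be estimated from it.

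The size depends on who sees what. For a list holder, foreknowledge is complete, but it matters only if that person can influence entry, which is not stated. For other unblinded staff, the 68% to 75% of correct guesses and 25% to 50% of certain assignments rest on two assumptions: fixed blocks of 2 to 6, and staff who track every earlier assignment. The order of baseline and allocation is an ambiguity to clear up, not a demonstrated error.

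**What to change.** 1. Replace the sentence on NBT and concealment with a statement that the sequence is concealed from everyone who screens, consents or judges eligibility. Keep the separate explanation of why patients and treating staff cannot be blinded.
2. Keep the list with the independent statistician, or with the contract research organisation that already monitors the trial (section 2.9.1).
3. Release each assignment singly, by web, telephone or sequentially numbered opaque sealed envelopes, and only after eligibility is signed off. Preferably do not disclose block sizes to the site.
4. State in section 2.2 that baseline ODI, NRS, EQ-5D, MPQ and RMDQ are completed before allocation is revealed.

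The parties needed are already involved, and sample size and treatments do not change. The cost is a small delay at visit 1.
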